### Outcomes

The following is pasted into the protocol directly from our NIMH grant application:

#### Outcome measures (\*denotes primary outcome measure)

| Outcomes                                                      | Operationalization of variable                                    | Timing of data collection after baseline |
|---------------------------------------------------------------|-------------------------------------------------------------------|------------------------------------------|
| i. Problem Solving Skills*                                    | Calculated problem solving index from SPSI-R                      | 6, 12 months                             |
| ii. Incident rate of moderate to severe symptomatic episodes* | QIDS score $\geq 11$ , corresponding to 'moderate' symptomatology | 2, 4, 6, 8, 10, 12 months                |
| iii. Depressive symptoms over time*                           | Mean QIDS scores over time                                        | 2, 4, 6, 8, 10, 12 months                |
| iv. Social and parenting functioning                          | Mean SAS-SR and PSI scores                                        | 6, 12 months                             |
| v. Receipt of mental health services                          | Standardized questionnaire                                        | monthly recall                           |
| vi. Head Start attendance                                     | Head Start records, analyzed as monthly absence rates             | monthly reports                          |

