### Background/Rationale/Purpose

Depression is common among young, low-income mothers and has negative repercussions on children. Additionally, this population of mothers lacks access to quality mental health services – making a prevention intervention potentially important. We are conducting a multi-year RCT of a Head Start-based intervention model developed as part of [name] and [name] K23 awards. PSE represents an integrated identification and intervention system based on the construct of screening, brief intervention, and referral to treatment (SBIRT). Within the case management services of Head Start, eligible mothers will be randomized to receive either usual care or PSE. The basic steps of PSE are: screening to determine the severity of one's depressive symptoms; a problem-solving intervention

for those at risk for depression; and referral to more definitive services for those initially in the at risk group, who have worsening symptoms over time.

The specifics of PSE have been modified and field-tested over the previous four years (primarily in Head Start, under another BUMC IRB protocol H-25084). Activated referrals to further care incorporate principles of motivational enhancement that have been demonstrated to improve engagement with care in other settings and for other medical conditions. We will conduct an efficacy RCT, involving 230 Head Start mothers. Over a 12-month follow up period, we aim to:

1. Improve mothers' problem solving skills (primary outcome)
2. Decrease the incident rate of episodes in which mothers experience moderate to severe depressive symptoms and reduce depressive symptoms over time (primary outcome)
3. Increase mothers' likelihood of engaging with primary care or specialty mental health services if referred (secondary outcome)
4. Improve parental functioning, as assessed by children's missed Head Start school days (secondary outcome).

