#### Summary of inclusion criteria

1. Family enrolled in Head Start, and child expected to attend Head Start activities for at least 6 months of the 12- month follow-up period.
2. Family without imminent plans to relocate
3. Mother is comfortable in English or Spanish.
4. Parent/guardian who has a child that attends Head Start
5. Child attending Head Start and is between the ages 0-5
6. Screen positive to 2-question depression screener (PHQ2), or have a past history of depression
7. Screen Negative for current MDE using the M.I.N.I MDE Module.
8. Ability to provide informed consent.
9. Not suicidal

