### Sample Size Justification

Based on empiric longitudinal data that we have collected among a cohort of Head Start mothers, we describe the size of detectable interventional effects with adequate statistical power for each primary outcome. All estimates assume 80% power and a two-sided alpha of 0.05.

- i. Problem solving skills. The mean problem solving (SPSI-R) score among mothers in our observational study is 12.2, (SD 2.5); women with  $\geq$  moderate depression symptoms have a mean score of 14.7 (SD 2.2) and those with  $\leq$  mild symptoms have a mean score of 9.8 (SD 2.8;  $p > 0.0001$ ). Using a two-sample t-test, a sample size of 100 per group will be able to detect a very granular one-point difference in mean SPSI-R scores between study groups (a standardized effect size of 0.4).

- ii. Incident rate of moderate to severe symptomatic episodes. Using poisson regression analysis, with 100 subjects in each study group and a poisson rate of 1.2 spikes per 5 follow-up assessments in the control group (according to our current data), we can detect a reduction in the rate of spikes to 0.8 in the treatment group – a 33% reduction in symptomatic episodes.
- iii. Depressive symptoms over time. In our longitudinal data, we have observed the following mean QIDS scores for each follow-up month and assume these values for the control group in the planned study: 8.2; 7.6; 7.5; 6.9; 7.2 (common SD, 5.9). We hypothesize that the following mean QIDS scores in the treatment group would be achievable and clinically significant: 7.2; 6.6; 5.5; 4.4; 4.2, resulting in a mean difference of 3 points in QIDS scores across study groups (note: a 3-point difference in QIDS scores, in the majority of cases, would move a subject across a clinical cutoff corresponding to mild, moderate or severe symptoms). Using a two group repeated measures design analyzed by generalized estimating equations or mixed linear models, noting within-subject correlations of 0.7 for values separated in time by one month and 0.6 for those separated for two months or more in our longitudinal analysis), we can detect the above differences in the means between groups over time with 100 subjects per study group.

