### Data Analysis

Our analysis plan conforms to CONSORT guidelines. We will record the number of families approached, screened, ineligible, and refusing participation. We will assess the success of randomization by comparing baseline characteristics between groups. We will record subject attrition and note all adverse events. To estimate intervention effect, we will conduct an intention-to-treat analysis to compare the difference between intervention and control groups for all primary and secondary outcome measures. The following primary outcomes will be analyzed accordingly:

- i. Problem solving skills. We will employ two sample t-tests to compare mean problem solving scores between groups. If significant baseline differences exist across groups, we will employ linear regression analysis to adjust for these differences.
- ii. Incident rate of moderate to severe symptomatic episodes. We will employ Poisson regression techniques to compare rates of elevations in QIDS scores to  $\geq 11$  (moderate symptomatology) over the 12 months of follow-up.
- iii. Depressive symptoms over time. We will use generalized estimating equations or mixed linear models to examine group-by-time effects on mean QIDS scores over the 12 months of follow-up.

Using generalized mixed models for each of these outcomes (to which the above analytic methods can be extended), we will also investigate the impact of Head Start enrollment site as a clustering effect. As an exploratory analysis, we will also examine additional clustering of PSE clients by educator.

This analysis plan, taken from our grant application, will be reproduced in our IRB application.

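### Primary outcome ii is called an incident rate of episodes, but as defined and powered it is the rate of assessments with QIDS at or above 11

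*Protocol*

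**What the plan says.** The protocol's Background/Rationale/Purpose section gives as a primary aim: "Decrease the incident rate of episodes in which mothers experience moderate to severe depressive symptoms". The Outcome measures table carries the label "Incident rate of moderate to severe symptomatic episodes", marks it as primary, and operationalises it as "QIDS score $\geq 11$ , corresponding to 'moderate' symptomatology", collected at months 2, 4, 6, 8, 10 and 12. Data Analysis states: "We will employ Poisson regression techniques to compare rates of elevations in QIDS scores" to 11 or more over the 12 months.

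Sample Size Justification assumes "a poisson rate of 1.2 spikes per 5 follow-up assessments in the control group" and says "we can detect a reduction in the rate of spikes to 0.8 in the treatment group", with 100 analysable mothers per group. Its concluding paragraph refers to incident rates of elevated QIDS scores.

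On entry, current subsyndromal symptoms are one of two routes into the trial (Details of Inclusion Criteria). The upper limit on depressive symptoms is "Screen Negative for current MDE using the M.I.N.I MDE Module"; no QIDS ceiling is set. QIDS is part of the baseline survey, but the protocol gives it no role in this outcome.

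**The concern.** An incident episode needs an onset: a score below the cut-off followed by one at or above it, with a rule for mothers already above it at the start. The protocol gives a cut-off and a list of months, and nothing more. Taken as written, a mother elevated at several consecutive assessments adds one to the count each time, including when she was already elevated at entry. The label and the definition then describe different quantities.

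This matters because the trial is presented as prevention. A lower count could arise because fewer mothers develop symptoms, or because symptoms present at entry or arising later resolve sooner. Both are worthwhile results, but only the first is a lower incidence of episodes. The definition also sets the number of events, and so the power. It should be fixed before the data are seen.

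**Working it through.** **Inputs (Sample Size Justification unless noted).** Rates of 1.2 and 0.8 per 5 assessments; 100 per group; "All estimates assume 80% power and a two-sided alpha of 0.05"; control mean QIDS 8.2, 7.6, 7.5, 6.9, 7.2 with SD 5.9; within-subject correlation 0.6 for values two months or more apart, which is the spacing of the planned assessments. The cut-off of 11 and the six follow-up months come from the Outcome measures table. The baseline QIDS distribution is not given and has to be assumed.

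**1. The plan's own power.** Wald comparison of two Poisson rates: power = Φ(difference / √(sum of rates / n) − 1.96) = Φ(0.4 / √(2.0/100) − 1.96) = Φ(2.83 − 1.96) = 80.7%. The required n is (1.96 + 0.8416)² × 2.0 / 0.4² = 98.1 per group. The stated 80% with 100 per group is reproduced.

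**2. What the 1.2 counts.** The expected number of elevated assessments out of 5 is the sum over the five control means of P(score at or above the cut-off):

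| Assumed distribution, SD 5.9 | Cut at 10.5 | Cut at 11 |
|---|---|---|
| Normal | 1.52 | 1.38 |
| Gamma | 1.19 | 1.09 |

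Counting only onsets would give about 0.5 to 0.7 per 5. The planning rate of 1.2 therefore fits a count of every elevated assessment.

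**3. How much of the count is continuation.** Per assessment, 1.2/5 = 24% are elevated. The model has a normal latent score, a threshold passed by 24%, correlation 0.6 between all assessments, and baseline plus six follow-ups. With baseline prevalence equal to follow-up prevalence, the mean count is 6 × 0.24 = 1.44, of which about 0.68 are onsets; (1.44 − 0.68)/1.44 = 53% follow an elevated assessment. The exclusion of a current major depressive episode should remove some high baseline scores. Truncating baseline QIDS is an illustrative way to allow for this:

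| Baseline QIDS | Counts following an elevated assessment | Counts from mothers elevated at baseline | Counts in an unbroken run from baseline |
|---|---|---|---|
| Not truncated | 53% | 53% | 28% |
| Below 15.5 | 46% | 41% | 18% |
| Below 12.5 | 37% | 20% | 8% |
| Below 11 | 31% | 0% | 0% |

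Using the protocol's own means instead of the 24% calibration moves the second column only modestly: 54% (gamma) or about 60% (normal) without truncation, 43-51% below 15.5 and 36-41% below 12.5. If no mother is elevated at baseline it is about 28-30%.

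**4. Power of an onset count.** Over 5 assessments, without truncation, onsets are about 1.2 × (1 − 0.53) = 0.564 per control mother. A one-third reduction gives 0.376. Power = Φ(0.188 / √(0.940/100) − 1.96) = Φ(1.94 − 1.96) = 49%. For 80% power, n = (1.96 + 0.8416)² × 0.940 / 0.188² = 209 per group.

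Steps 1 and 4 treat counts as Poisson, as the plan does.

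**The case against.** Four objections deserve an answer.

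*The counting rule is inferred.* The table gives a threshold and months, the sample size section speaks of spikes, and Data Analysis speaks of elevations to 11 or more, which can be read as upward crossings. How consecutive elevations are handled could also be left to a statistical analysis plan that is not shown. It stands that no explicit counting rule can be quoted, so a flat statement that an always-elevated mother contributes six incident episodes holds under one reading only. But no crossing rule is given either, and the planning rate fits the all-assessments reading (step 2). The mismatch between label and definition is in the protocol's own text.

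*The size depends on the baseline.* A reader might infer that about half of the counted episodes are continuing symptoms. The documents do not support that as a fact. The 24% comes from an observational cohort that is not stated to have excluded major depressive episodes, whereas the trial does. Nor does the protocol's correlation of 0.7 justify a higher figure, since it is given for one-month spacing. This objection stands.

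*Following an elevated assessment is not the same as symptoms carried over from entry.* Some such runs begin after randomisation. Only an unbroken run from baseline is simply entry symptoms continuing, and that share is 0-28%. A reader might infer that a benefit could come wholly from faster remission of entry symptoms; that is an extreme case, and 'partly' is what can be said.

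*The arms are comparable.* Randomisation is 1:1 and stratified by depression history, so baseline elevation is balanced on average. A reader might infer a biased comparison; there is none. Omitting a baseline covariate from a protocol is not in itself an error. Symptom reduction is also a stated primary aim, with mean QIDS as its own primary outcome.

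**Conclusion.** The point holds as one of definition and interpretation. Outcome ii is labelled as incidence of episodes, but as defined and powered it is the rate of scheduled assessments with QIDS at or above 11. A lower rate could partly reflect quicker remission.

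Under the normal threshold model (24% elevated, correlation 0.6), roughly 30-55% of counted elevations would follow an elevated assessment and 0-28% would be an unbroken run from baseline. The upper ends need baseline prevalence equal to follow-up prevalence; the lower ends need no mother to enter at or above 11, which the eligibility criteria do not ensure. The mismatch itself depends on none of these figures.

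The stated power is right for the count that was powered. Between the arms the issue is precision only: in the same model, baseline QIDS explains about 20-40% of the variance of the count.

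**What to change.** Keep the powered count as the primary outcome, and name and report it as the number of scheduled follow-up assessments with QIDS at or above 11. Make the label consistent in Background/Rationale/Purpose, the Outcome measures table, Sample Size Justification and Data Analysis. Include baseline QIDS as a covariate in the Poisson model.

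Add one pre-specified supportive count of onsets: QIDS below 11 at the preceding assessment, baseline included, then 11 or more. Reserve the word 'incident' for that count.

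The cost is a change of wording, one covariate and one extra analysis, all on data already planned. The supportive count has about half as many events (0.68 against 1.44 per control mother over six assessments). At 100 per group it has about 49% power for the same 33% reduction, so it should be labelled as not powered.

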  - d. For those individuals who refuse screening, are not eligible or opt not to participate, we will record only their temporary study code on the recruitment screen. We will submit this list of temporary study codes to Head Start personnel for two reasons: 1) to avoid inadvertent re-approaching; and 2) so that Head Start can supply the study team with an anonymized demographic description of this population with a de-identified list of demographic characteristics, (Attached in the study binder). Specific variables will include only those that Head Start keeps for programmatic reasons (the equivalent of existing clinical data): age, language spoken, place of birth, race, ethnicity, education, work status, marital status, household type (single or double-headed household), number of people in household, living situation, income, health insurance status, type of government assistance.
4. Written Informed Consent: After the two screens are administered and the potential subject is found to be eligible, the subject will be enrolled (if willing) into either the RCT or into a small supplemental pilot study of 'PSE Lite.' Immediately following the signing of the consent form, the following will happen:
- a. Subjects will be administered either the MacCAT-CR immediately after the consent form in order to ensure that subjects with limited cognitive capacities and/or major mental illness, including psychosis, are safeguarded from being in the study.
  - b. Subjects will be screened for suicidal ideation in order to safeguard subjects with high suicidal ideation. Our crisis protocols will be activated as necessary (Crisis Management Plan, Domestic Violence Protocol, Referral of Clients with Trauma or Substance Use – each protocol is provided in the study binder).
5. Once participants have completed the safeguards outlined in above, we will collect the following data from all mothers enrolled in the study *prior to* randomization. The interviews will be completed in private rooms at the Head Start center, or in subjects' homes (subjects' choice). The Baseline Survey will comprise the following valid and reliable scales:
- a. Children with Special Health Care Needs Screener

- b. Perceived Stress Scale
  - c. M.I.N.I. Depression Module (current or recurrent Major Depressive Episode (We will use the data from the second verbal screen for this. We have added this permission to the written consent form.))

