  - d. Quick Inventory of Depressive Symptoms. Beck Anxiety Inventory
  - e. Mental Health Service Use questions (adapted from Collaborative Psychiatric Epidemiology Surveys)
  - f. Medical Outcomes Study – Social Support Survey
  - g. Social functioning (Social Adjustment Scale-Self Report)
  - h. Problem Solving Questions (Social Problem Solving Inventory)
  - i. Substance Use (CAGE-AID and AUDIT)
  - j. Coping Questions (Brief COPE)
  - k. Rosenberg Self-Esteem Scale
  - l. Behavioral Activation for Depression Scale
  - m. Pearlin Mastery Scale
  - n. Stressful Life Events Questionnaire
  - o. Modified PTSD Symptom Scale
  - p. Demographics
  - q. Behavioral Activation Score
6. If randomized to the PSE group, we will employ a team of 4 to 6 research staff (at any given time) to serve as interventionists (referred to as educators or providers). The educators will deliver up to 6 PSE sessions with their clients, each session expected to take 30-45 minutes. Sessions will be delivered either weekly or biweekly, according to the wishes of the subject – with a full course of PSE expected to last 8 weeks. Sessions will be delivered at a location of the subject's choosing. In addition to PSE, intervention subjects will be periodically screened with the PHQ-9 as part of 3 out of the 6 PSE sessions. A score of 15 or greater will require the educator to refer the mother to more definitive mental health care. These referrals will be "activated," meaning that the PSE educators will employ motivational interviewing techniques to help the mothers follow through with the referrals. Lastly, educators will phone their clients monthly to conduct brief "booster session" check-in's.
- Request to audiotape a randomly selected PSE will be embedded in the initial consent form; this will be offered to all subjects for the sake of monitoring treatment fidelity. It will be made clear that subjects can refuse audiotaping but still partake in the rest of the study.
7. Control group: We have chosen our control group to best approximate "usual care" in Head Start. Thus, families will be followed by their Head Start caseworkers, and screened periodically for depression when deemed necessary by Head Start staff, per their usual routine. Referrals will be made

according to criteria specified in the grant application.

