8. Outcome assessments: Each subject will have a 12-month follow up period, during which blinded research assistants will assess outcome measures. Follow-up data collection will begin 2 months after baseline because a full, 6-session course of PSE typically lasts 6-8 weeks. To limit attrition, we will employ a combination of monetary incentives and postcard reminders. Through these strategies, approved by the BUMC IRB in our pilot work, we have been able to maintain follow up rates > 85% across all relevant ongoing studies (there is a separate section on participant compensation in the protocol manual).

Baseline, 6-month, and 12-month assessments will take place in person with a staff RA. We will administer the QIDS and mental health service use questions on a bimonthly basis throughout the study period, and this will be done by telephone by a staff RA.

The 6-month interview will comprise the following valid and reliable scales:

- a. Perceived Stress Scale
- b. M.I.N.I. Depression Module
- c. QIDS
- d. Mental Health Service Use questions (adapted from Collaborative Psychiatric Epidemiology Surveys)
- e. Social functioning (Social Adjustment Scale-Self Report)
- f. Parenting Stress Index
- g. Problem Solving Questions (Social Problem Solving Inventory)
- h. Coping Questions (Brief COPE)
- i. Pearlin Mastery Scale
- j. Behavioral Activation for Depression Scale
- k. Rosenberg Self-Esteem Scale

The 12-month interview will comprise the following valid and reliable scales:

- a. Perceived Stress Scale
- b. M.I.N.I. Depression Module
- c. QIDS
- d. Mental Health Service Use questions (adapted from Collaborative Psychiatric Epidemiology Surveys)
- e. Social functioning (Social Adjustment Scale-Self Report)
- f. Problem Solving Questions (Social Problem Solving Inventory)
- g. Coping Questions (Brief COPE)
- h. Pearlin Mastery Scale
- i. Behavioral Activation for Depression Scale
- j. Rosenberg Self-Esteem Scale
- k. Recent Life Changes Questionnaire

- I. Mood, anxiety and alcohol and other substance use, modules of the SCID

RA's will be trained not to leave telephone messages, and to introduce themselves as from "BMC" so as to ensure confidentiality.

9. At 6-months post randomization, parents and Head Start teachers will be asked to fill out the Social Skills Rating System (SSRS) with reference to all 3-5 year-old Head Start children of enrolled parents.
10. We will assess rate of absenteeism from Head Start for children of mothers who are in our study.

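### The outcome table schedules the Parenting Stress Index at 6 and 12 months, but the interview lists include it at 6 months only

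*Protocol*

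**What the plan says.** Protocol, Outcomes, outcome measures table: row iv, social and parenting functioning, is operationalized as "Mean SAS-SR and PSI scores". The column headed "Timing of data collection after baseline" gives 6 and 12 months for this row. The row has no asterisk, so it is not a primary outcome.

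Protocol, Procedure, item 8 (outcome assessments): the 6-month interview includes "f. Parenting Stress Index". A second list follows under the words "The 12-month interview will comprise the following valid and reliable scales"; it runs from a to l and does not name the PSI. Between the in-person visits, the plan is: "We will administer the QIDS and mental health service use questions on a bimonthly basis throughout the study period". Nothing else is assigned to those calls.

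Protocol, Data Analysis: an intention-to-treat comparison between the groups is planned for every primary and secondary outcome measure.

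**The concern.** The outcome table says what the trial will report, and the interview lists say what the research assistants will collect. For the 12-month PSI the first makes a promise that the second does not support. A statistical analysis plan cannot repair this later, because it concerns whether a questionnaire is given at all.

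Two things are at stake. First, the PSI is the only parenting questionnaire in the outcome table that is completed by the mother, so without a 12-month score the trial cannot show on that scale whether a 6-month effect lasts. Second, someone comparing a trial report with row iv would find a 12-month result missing and could not tell a protocol inconsistency from selective reporting.

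**Working it through.** The protocol gives no figure to reproduce here; the check is an item-by-item comparison of row iv with each contact under Procedure.

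| Contact | PSI required by row iv | PSI listed | SAS-SR required by row iv | SAS-SR listed |
|---|---|---|---|---|
| Baseline (a to q) | no | no | no | yes, item g |
| Bimonthly calls | no | no | no | no |
| 6 months (a to k) | yes | yes, item f | yes | yes, item e |
| 12 months (a to l) | yes | **no** | yes | yes, item e |

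Tally: the PSI is covered at 1 of 2 required times and the SAS-SR at 2 of 2. Row iv therefore has 3 of its 4 instrument-by-time cells.

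**Could the gap come from the reading of the PDF?** The 6-month list has 11 lettered items. The 12-month list repeats 10 of them in the same order and adds two (recent life changes and the SCID modules): 11 − 1 + 2 = 12, which matches the letters a to l with no gap. The one instrument dropped between the two lists is the PSI. The problem-solving inventory moves up from g to f, the letter that the PSI holds at 6 months. No lettered item has been lost.

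**Could the PSI be present under another name?** The Perceived Stress Scale appears at baseline, 6 and 12 months, but at 6 months it stands in the same list as the Parenting Stress Index, so the two are different instruments. Row i speaks of a problem solving index, but row iv concerns parenting, and the Parenting Stress Index is the instrument in the lists that fits its label. The Social Skills Rating System (Procedure, item 9) is collected at 6 months and describes the child.

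**Could another contact supply it?** The bimonthly calls carry the QIDS and the service-use questions only.

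**Is the table superseded text?** The Outcomes section says that it was pasted from the grant application. That may explain how the mismatch arose, but the table is the protocol's current statement of outcomes and not a record of changes.

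**The case against.** The strongest reply is that the lists are not a dependable inventory. The Risks and Discomforts section says that all clients are asked domestic violence questions, yet no list names them, and the baseline list seems to enter behavioral activation twice. The instruments themselves are in the study binder, which is not at hand, so the 12-month booklet may contain the PSI after all. This stands as a limit on the consequence: the text shows a contradiction, not that the data will certainly go uncollected. It does not remove the contradiction.

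Three stronger readings are tempting, and the protocol does not support them.

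- *That the missing baseline PSI is also an error.* The Baseline Survey list does omit it, but the table's timing column covers collection after baseline only, so no baseline score is promised. A randomized comparison of 6-month means is valid without one. A baseline score would allow adjustment, change scores and a balance check, but the protocol states no baseline-adjusted analysis of the PSI. It gives within-subject correlations for the QIDS only, so the gain in precision cannot be sized from this document.
- *That the trial could say nothing about whether a parenting effect lasts.* Background/Rationale/Purpose assesses parental functioning by children's missed Head Start days, and row vi of the table collects absences monthly. Only durability on the PSI is lost.
- *That a headline outcome is damaged.* Row iv is unstarred, and the two outcomes that Background/Rationale/Purpose labels secondary are engagement with services and missed school days. Neither is the PSI.

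**Conclusion.** The inconsistency is real and narrow. Row iv calls for PSI scores at 6 and 12 months, and the interview lists provide for 6 months only. On the assumption that the lists are followed as written, the 12-month PSI component of this non-primary outcome will have no data: one of two planned PSI time points. The SAS-SR half of row iv is complete, the 6-month PSI comparison remains valid, and no primary outcome or sample-size calculation depends on the point. It should still be corrected, because the protocol now commits to a comparison that its own schedule does not feed.

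**What to change.** Make Procedure, item 8 and row iv of the outcome table agree.

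- **Preferred:** add the Parenting Stress Index to the 12-month interview list. The cost is one more questionnaire at an interview that is already planned and, under Payment, already compensated. The protocol gives neither the version nor the length of the PSI, so the added time cannot be stated from it.
- **If that is not feasible, or those visits have passed:** change row iv to read SAS-SR at 6 and 12 months, PSI at 6 months only, and make no 12-month parenting-stress claim. The cost is one edited table row.

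If the binder's 12-month instrument already contains the PSI, correcting the list in the protocol is enough. Adding the PSI at baseline is optional: it could improve precision for mothers not yet enrolled, but it is not needed to make the lists match row iv.

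### Outcome v counts receipt of mental health services without separating new care from care already under way, and a null result on it cannot be read as failure of Aim 3

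*Protocol*

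**What the plan says.** - **Aim.** The third aim in Background/Rationale/Purpose, a secondary outcome, is to raise mothers' "likelihood of engaging with primary care or specialty mental health services if referred".
- **Outcome.** The only listed outcome that could serve this aim is row v of the Outcome measures table, "v. Receipt of mental health services". It is operationalized as a standardized questionnaire with monthly recall. The row carries no condition of new care, need or referral.
- **Analysis.** The Data Analysis section uses intention to treat to "compare the difference between intervention and control groups for all primary and secondary outcome measures". It gives methods only for the three primary outcomes, and mentions baseline adjustment only for problem-solving scores.
- **Eligibility.** A mother qualifies if she meets this criterion: "Screen positive to 2-question depression screener (PHQ2), or have a past history of depression". Neither the inclusion nor the exclusion criteria, in summary or in detail, rule out current mental health treatment short of a current major depressive episode.
- **Data collected.** The Baseline Survey in the Procedure section includes "Mental Health Service Use questions (adapted from Collaborative Psychiatric Epidemiology Surveys". The same questions recur bimonthly with the QIDS. The document gives the baseline answers no role in analysing row v.
- **Expected effects.** Sample Size Justification, item ii, takes a control rate of 1.2 episodes falling to 0.8 under PSE, "a 33% reduction in symptomatic episodes". In the PSE arm only, educators screen at three sessions ("A score of 15 or greater will require the educator to refer the mother to more definitive mental health care") and use motivational techniques to help mothers follow through.

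**The concern.** Two features of row v make it a weak measure of engagement.

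First, a mother with a depression history may already be seeing a provider when she is randomized. If she continues, she counts as having received services whichever arm she is in. She cannot be newly engaged, so she adds noise and no contrast.

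Second, the row has no fixed favourable direction. If PSE prevents episodes, fewer PSE mothers need services and receipt falls. If activated referrals work, more of those in need obtain services and receipt rises. The whole-arm comparison gives only the net result. A flat row v could mean that engagement did not improve, or that it improved while episodes were also prevented. Reporting the first when the second is true would misstate Aim 3.

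**Working it through.** **The plan's own figure.** The protocol gives no rate or power for outcome v. The nearest figure is the Poisson calculation: n per arm = (1.960 + 0.842)² × (1/1.2 + 1/0.8) / [ln(0.8/1.2)]² = 99.5, so 100. This reproduces the stated 100 per group.

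**Sample.** 230 × 0.85 = 195.5 mothers after the stated 15% attrition, or 97 per arm. Alpha is two-sided 0.05.

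**Dilution by care under way**

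Assumptions not in the document: a share *b* is in care at entry and all of them stay in it; new engagement among the rest is 10% in control and 25% in PSE.

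- Any receipt = *b* + (1 − *b*) × new engagement. The difference is (1 − *b*) × 15 points.
- New receipt among baseline non-users: 10% against 25%, with 97 × (1 − *b*) per arm.
- Power = Φ[(d − 1.96 × SE0)/SE1], with SE0 from the pooled proportion and SE1 from the separate ones.

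Worked case, *b* = 15%: 0.15 + 0.85 × 0.10 = 0.235 and 0.15 + 0.85 × 0.25 = 0.3625, so d = 0.1275. SE0 = 0.0657 and SE1 = 0.0651. Power = Φ[(0.1275 − 0.1288)/0.0651] = 0.49.

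| Already in care | Any receipt, control v PSE | Power, any receipt | Non-users per arm | Power, new receipt |
|---|---|---|---|---|
| 5% | 14.5% v 28.8% | 68% | 92 | 77% |
| 10% | 19.0% v 32.5% | 58% | 87 | 75% |
| 15% | 23.5% v 36.3% | 49% | 82 | 72% |
| 25% | 32.5% v 43.8% | 36% | 73 | 67% |
| 35% | 41.5% v 51.3% | 27% | 63 | 60% |

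The subset is smaller but more powerful throughout, because the mothers left out contribute no contrast under these assumptions.

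**Opposing directions**

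Under the protocol's Poisson rates, the share with at least one episode is 1 − e^(−1.2) = 69.9% in control and 1 − e^(−0.8) = 55.1% in PSE. Assume that only these mothers start services and that nobody is in care at entry.

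- Engagement given an episode of 30% v 45% (assumed): receipt is 0.699 × 0.30 = 21.0% v 0.551 × 0.45 = 24.8%, power about 9%.
- Engagement of 40% v 60% (assumed): receipt is 28.0% v 33.0%, power about 12%.

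Engagement rises by half in each case, yet receipt moves by only 4 to 5 points. The break-even rise is 0.699/0.551 = 1.27-fold: a smaller improvement in engagement would leave PSE with lower receipt than control.

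**The case against.** **The derivation may be in a SAP.** The row does not say ever or never, or that care under way counts; that is inferred from the absence of any restriction. How a secondary variable is derived, and which covariates enter its model, is often left to a SAP, and new receipt can already be derived from the data collected. This stands, and it is why the point is an improvement and not an error. It does not remove the direction problem, which baseline adjustment cannot cure.

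**Total receipt is a legitimate intention-to-treat outcome, with outcome ii reported beside it.** This also stands. What is needed is that the plan says row v is to be read that way.

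**Few mothers may be in care.** The protocol says that this population lacks access to quality mental health services and that only a small minority of such women receive the care they need, and it excludes current major depressive episodes. The 5% to 10% rows of the table are therefore plausible, and there the loss of power is about 9 to 17 points.

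**Two stronger readings that the document does not support.** A reader might infer that prevention and engagement cancel exactly. That follows only if the 33% reduction, which is a reduction in the episode rate, is applied to the share of mothers ever elevated. With 50% falling to 33% and engagement of 30% v 45%, receipt is 15% in both arms. Under the protocol's Poisson rates the share ever elevated falls by 21%, and the cancellation is partial.

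A reader might also infer that row v should be replaced by a measure of unmet need, such as QIDS of 11 or more with no service by the next contact. That measure mixes the same two pathways. With 50% falling to 33% elevated and engagement fixed at 30% in both arms, it drops from 0.50 × 0.70 = 35% to 0.333 × 0.70 = 23% by prevention alone, with power about 43%. It is also undefined at month 12, which has no next contact.

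**Conclusion.** The concern holds as a low-priority improvement to a secondary outcome. As listed, row v can count continuing care in both arms, which scales any difference by one minus the share already in care. At 10% v 25% new engagement, the cost in power against new receipt among non-users is about 9 points at 5% in care (68% v 77%), 23 at 15% (49% v 72%) and 33 at 35% (27% v 60%). These sizes depend on assumed engagement rates, an assumed share in care, and baseline users all remaining in care.

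The opposing directions follow from the protocol's own hypotheses; only their size needs assumptions. A null or negative row v is therefore not evidence that Aim 3 failed.

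**What to change.** 1. Analyse row v in all randomized mothers, adjusted for or stratified by the service use recorded at baseline.
2. Beside it, report new receipt among mothers with no service use at baseline. This subset is fixed before randomization, so the randomized comparison is kept. It addresses dilution only: prevention can still lower new receipt.
3. State that row v is a total effect, which fewer episodes can lower and better engagement can raise, and that a null or negative result is to be read alongside outcome ii and not taken as failure of Aim 3.
4. If an unmet-need measure is wanted, label it exploratory, define how month 12 is handled, and do not let it replace row v.

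**Cost.** A few sentences in the outcome table and analysis section, fixed before unblinding. No new data are needed, since service use is asked at baseline and with the QIDS at follow-up. The downside is the smaller subset, for example 82 per arm instead of 97 if 15% are already in care.
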